# Clinical utility of elective paediatric flexible bronchoscopy and impact on the quality of life: protocol for a single-centre, single-blind, randomised controlled trial

**DOI:** 10.1136/bmjresp-2023-001704

**Published:** 2024-02-26

**Keywords:** Bronchoscopy, Paediatric Physician

## Abstract

**Introduction:**

Elective flexible bronchoscopy (FB) is now widely available and standard practice for a variety of indications in children with respiratory conditions. However, there are no randomised controlled trials (RCTs) that have examined its benefits (or otherwise).

Our primary aim is to determine the impact of FB on the parent-proxy quality-of-life (QoL) scores. Our secondary aims are to determine if undertaking FB leads to (a) change in management and (b) improvement of other relevant patient-reported outcome measures (PROMs). We also quantified the benefits of elective FB (using 10-point Likert scale). We hypothesised that undertaking elective FB will contribute to accurate diagnosis and therefore appropriate treatment, which will in turn improve QoL and will be deemed to be beneficial from patient and doctor perspectives.

**Methods and analysis:**

Our parallel single-centre, single-blind RCT (commenced in May 2020) has a planned sample size of 114 children (aged <18 years) recruited from respiratory clinics at Queensland Children’s Hospital, Brisbane, Australia. Children are randomised (1:1 concealed allocation) within two strata: age (≤2 vs >2 years) and indication for FB (chronic cough vs other indications) to either (a) early arm (intervention where FB undertaken within 2 weeks) or (b) delayed (control, FB undertaken at usual wait time). Our primary outcome is the difference between groups in their change in QoL at the T2 timepoint when the intervention group has had the FB and the control group has not. Our secondary outcomes are change in management, change in PROMs, adverse events and the Likert scales.

**Ethics and dissemination:**

The human research ethics committee of the Queensland Children’s Hospital granted ethical clearance (HREC/20/QCHQ/62394). Our RCT is conducted in accordance with Good Clinical Practice and the Australian legislation. Results will be disseminated through conference presentations, teaching avenues, workshops, websites and publications.

**Registration:**

Australia New Zealand Clinical Trial Registry ACTRN12620000610932.

WHAT IS ALREADY KNOWNElective flexible bronchoscopy (FB) is now a routine procedure undertaken in children as part of the investigatory pathway when the child has respiratory symptoms/signs and/or diseases. However, the frequency of its use differs among centres which is possibly related to the current lack of high-level evidence for its use.WHAT THIS STUDY ADDSOur study will be the first randomised controlled trial (RCT) to evaluate the clinical utility of elective FB in children and its impact on patient-related outcomes.HOW THIS STUDY MIGHT AFFECT RESEARCH, PRACTICE OR POLICYOur study will provide the first high-level evidence in the field of paediatric FB. If our hypotheses are correct, our RCT may influence national and international clinical practice, especially in centres where FB is very commonly or uncommonly undertaken.

## Introduction

Flexible bronchoscopy (FB) involves viewing the larynx and lower airways with a flexible bronchoscope. Bronchoalveolar lavage (BAL) is usually performed at the time of FB. BAL provides various details including cellular profile and microbiology of pathogens. It is primarily used in children for diagnostic purposes and sometimes is also therapeutic.^1 2^ FB is commonly used in many paediatric respiratory centres around the world in the acute/emergency settings as well as in the non-acute (or elective settings) to help in the diagnosis and guide management in patients with respiratory symptoms, for example, chronic cough, recurrent croup and recurrent wheeze.^3^ However, the frequency of its use differs among centres, particularly in the elective settings, the focus of this study.

The publications^1 2^ on the indications, contraindications and complications of using FB in children are based on expert opinion and/or retrospective studies. Indications for undertaking FB are varied and include examination of the laryngo-tracheobronchial tree for structural and congenital airway lesions that contribute to, or the cause of, respiratory symptoms (eg, stridor/noisy breathing, persistent/recurrent wheezing, persistent radiographic abnormality, chronic cough and haemoptysis) and therapeutic indications (eg, evaluation/removal of foreign body or mucus plugs).^4^ Information gained from undertaking non-urgent FB arguably lead to attaining an accurate diagnosis (eg, diagnosis of tracheobronchomalacia in children with chronic wheeze^5^ and identification of bacterial infection).^6^ As diagnostic clarity leads to appropriate management and improvement of symptoms, the quality of life (QoL) of patients and/or their parents should improve following undertaking FB.

Currently, there are no randomised controlled trials (RCTs) examining the utility of elective FB in children with respiratory conditions. Indeed, two international thoracic societies (American Thoracic Society^7^ and European Respiratory Society)^4^ highlight the paucity of prospective studies and the absence of any RCTs examining the utility of FB in children. This is a critical knowledge gap, as FBs in children are usually undertaken using general anaesthesia with its associated risks of adverse events in addition to those from FB itself (eg, hypoxia, nausea, vomiting, headaches, confusion and unscheduled hospitalisation).^8^ Cost implications to the health system and the family are significant. For the usual day-only admissions, the mean cost is $A6071 (95% CI 5271 to 6871).^9^

Several retrospective studies have demonstrated that FB is a useful tool in children with persistent wheezing^10–12^ or ‘difficult to treat asthma’^5^ with a definitive diagnosis made in 57%–85% of cases.^10 11^ FB has been shown to provide diagnosis and change management in the evaluation of infants with stridor (33.9% of patients diagnosed with laryngomalacia and 49.5% of patients diagnosed with secondary airway lesions).^13^ FB and BAL are useful in immunocompetent children with unexplained infiltrates on chest radiographs leading to specific diagnosis in 30% of patients,^14^ as well as immunosuppressed children (diagnostic in 65.1% of patients and the antimicrobial treatment changed for 56.8%of patients).^15^ Furthermore, a specific diagnosis was made in almost 89.8% of children with congenital cardiac disease^16^ and 33% of children with unexplained recurrent and persistent pneumonia,^17^ after bronchoscopic evaluation. In another retrospective review consisting of 149 children, FB was described as a crucial diagnostic (confirming, ruling out and discovering unexpected diagnosis) and therapeutic tool.^18^

FB has also been shown to be useful in the diagnosis and management of neonates in the neonatal intensive care unit (ICU) where an abnormality was detected in 87.5% of FBs^19^ performed in neonates with noisy respiration and increased work of breathing or persistent need for respiratory assistance or persistent radiological opacities. The most common abnormalities found in neonates were tracheobronchomalacia, laryngomalacia, subglottic stenosis, choanal atresia, laryngeal cleft and tracheoesophageal fistula.^19^ FB has a high yield in children admitted to the paediatric ICU where 68% of diagnostic FBs were deemed to be abnormal, including 16% having significant extraluminal obstruction, 24% having new findings of airway anomalies and 14.5% showing endotracheal tube misplacement. Further positive microbiological results which altered or confirmed changes in patient management occurred in 46.1% of children who had a BAL during their FB in ICU.^20^ FB has also been shown to have a complementary role in the diagnosis of foreign body aspiration with a diagnostic accuracy rate of 100%, and 40% of cases were negative which stopped the operation and alleviated the need for a rigid bronchoscopy and further procedural risks.^21^

There are few prospective studies. One prospective study involving 56 indigenous children newly diagnosed with bronchiectasis (BE) found there were 25 occasions where FB and BAL altered clinical management in 23 children.^6^ A systematic review assessing the utility of FB for critically ill children (ie, non-elective FB) included 4706 patients from 27 studies (3 studies included patients above age 18 years, and none were RCTs).^22^ The authors described that using FB led to a change in medical management in 28.9% (range 21.9%–69.2%) of children.

FB is not a procedure without risk, with adverse events such as fever, hypoxia, excessive coughing, laryngospasm, epistaxis, bronchospasm and rarely pneumothorax.^8^ Therefore, it is crucial to evaluate the benefits of this procedure on clinical outcomes and patient-related outcome measures (PROMs), for example, QoL and assessing whether it leads to a change in clinical management, through the rigour of RCT. Different centres have different approaches resulting in vast differences in the number of FBs undertaken. The availability of robust evidence about the utility of FB may change clinical practice, possibly either increasing FBs utilisation in centres where FB is infrequently undertaken or reducing FBs in centres where FB is frequently used.

There is thus a need to obtain high-quality evidence to define the efficacy, benefits and adverse events associated with elective FB in the diagnosis and management of children with respiratory conditions to improve clinical outcomes for children. The ideal RCT to assess the benefits of elective FB is a randomisation to undertaking elective FB or no FB/sham FB. However, this is not ethically possible as FB has now become the standard of care.^7^

### Study objectives and hypothesis

Our primary question is as follows: among children undergoing elective FB, does this procedure lead to improvement in parents’ proxy QoL, using the age-specific Pediatric Quality of Life Inventory 4.0 (PedsQL 4.0)?^23^ We hypothesise that undertaking FB for diagnosing their child’s underlying condition leads to improved QoL in parents.

Our secondary aims are to:

Determine if FB leads to change in management based on a priori definitions (see below).Determine if FB improves parental depression, anxiety and stress scale (DASS21)^24^ and/or the State-Trait Anxiety Inventory (STAI)^25^ scores and in the subset of children who have cough, the Parent-proxy Children’s Acute Cough-specific QoL (PAC-QoL)^26^ and cough severity scores^27^
Quantify the benefits (parent and doctor perspectives) of elective FB assessed by 10-point Likert scales^28^

Our secondary hypotheses is that FB will lead to:

Management decisions based on the a priori definitions which will lead to appropriate treatmentImproved PROMs (STAI,^25^ DASS21^24^ scores and/or PAC-QoL^26^ and cough severity scores,^27^ in the subset with cough)

We further hypothesised that FB will be deemed to be beneficial from both the patient and the doctor perspective.

## Methods and analysis

### Study setting and design

We are conducting a waitlist parallel, single-centre (Department of Respiratory and Sleep Medicine at the Queensland Children’s Hospital (QCH), Brisbane, Australia), single-blinded RCT with concealed allocation to determine the impact of paediatric FB on QoL and change in management. FB and BAL are done in a standard manner in the unit as per our previous studies.^29^ In our hospital, obtaining BAL is standardised.^30 31^ Further information about BAL procedures are provided in online supplemental file 1. Figure 1 summarises our study design and is in accordance with the recommendations of the Standard Protocol Items Recommendations for Interventional Trials guidelines.^32^ We recruited our first participant on 27 May 2020, and the study is ongoing with an anticipated completion of recruitment by late 2023 and complete follow-up by mid-2024.

10.1136/bmjresp-2023-001704.supp1Supplementary data

**Figure 1 F1:**
[figure not shown]
Schematic study design of the RCT. PROM, patient-related outcome measure; PedsQL 4.0,^23^ Pediatric Quality of Life Inventory 4.0; DASS21,^24^ depression, anxiety and stress scale; STAI,^25^ State-Trait Anxiety Inventory; PAC-QoL,^26^ Parent-proxy Children’s Acute Cough-specific Quality of Life; QoL, quality of life; FB, flexible bronchoscopy; BAL, bronchoalveolar lavage; T1, timepoint 1; T2, timepoint 2; T3, timepoint 3; T4, timepoint 4; T5, timepoint 5.

### Patient and public involvement

Parents/guardians of patients were first involved in the preliminary study design as the study was partially based on the experience, suggestions and preferences from parents/grandparents whose children had or planned to have an elective FB. The parents/guardians of the children undergoing FB agreed with the waitlist design while being blinded to allocation. This is reflected by only one parent who has declined to participate in the study to date. We have also presented the study design to members of our parent advisory group (https://www.crelungs.org.au/cre-parent-and-community-advisory-group), and they were supportive of the study. We did not directly assess the burden of the parents’ participation in this study, but we assessed their opinion on the benefits of FB. Also, the patients were able to report any burden and could withdraw at any time. Our outcome measures included appropriate PROMs. We plan to disseminate the study outcomes to study participants during their follow-up clinical reviews through a leaflet with a summary of what our study found. We will disseminate study results to the wider community through this publication, future workshops and education sessions to health professionals, to highlight the utilisation of undertaking elective FB in children.

### Study population

Our inclusion criteria are (1) children referred to the paediatric respiratory outpatient clinic of QCH in Brisbane who require FB as deemed by the child’s primary respiratory as part of the routine clinical practice, (2) aged <18 years, (3) parents/guardian planning to remain at the study site for >6 months, (4) parents/guardians who provide informed consent able to complete the PROM questionnaires and (5) children who have not had FB previously.

Our exclusion criteria are (1) urgent FB required (eg, examination of severe stridor on child in intensive care), (2) previously enrolled or (3) limited English literacy skills.

### Recruitment

Parents/guardians of children attending QCH respiratory clinics, who are deemed to need an elective FB as part of the child’s routine investigations and who satisfy the aforementioned eligibility criteria, are approached by the primary author ([name]) either in a clinic or over the phone. The study is discussed with the parents/guardians (hereafter called parents), and a parent information sheet is provided. After informed written consent is obtained, the child is recruited, data are collected and the child is randomised into one of the two study arms as per below.

### Randomisation and allocation

Randomisation is stratified by as follows: (a) indication for FB (chronic cough or other indications (recurrent stridor, recurrent wheeze, haemoptysis, recurrent pneumonia, persistent radiographic changes, suspicion of foreign body, unexplained dyspnoea and others) and (b) age (≤2 or >2 years). The computer-generated permuted block (block size 4–6) randomisation allocation sequence (1:1 ratio) was prepared by an independent person not involved in the study. After informed consent, children are randomised to one of the two arms: (1) intervention group where the FB occurs early or (2) control group where the FB occurs within the normal waiting time. Parents of participants will not be informed of the usual wait times; thus, they are unaware of whether they are in early or ‘usual-wait’ group and hence will remain blinded. Blinding the physician is not possible.

### Overview of procedures for intervention and control groups

The outline of study procedures for both control and intervention groups is summarised in figure 1 and table 1. At enrolment (timepoint 1 (T1), baseline), both groups complete the various PROM questionnaires, that is, STAI, DASS21 and PedsQL 4.0. PAC-QoL (including cough severity scores) is also completed if chronic/recurrent cough is the indication for FB. All the PROM questionnaires are filled out by the parents/guardians. Children aged ≥5 years also complete a PedsQL 4.0 questionnaire. The intervention group (early-group) has their FB undertaken within 1–2 weeks of enrolment (followed by a phone call 48–72 hours after). At timepoint 2 (T2), children in the intervention group are seen in a follow-up clinic 2–3 weeks after their FB, and their parents repeat the PROM questionnaires, while the control group also repeat the PROM questionnaires (prior to their FB, ie the control group has not had their intervention yet at this timepoint) (see figure 1, table 1). At timepoint 3 (T3), the control group has their FB (followed by a phone call 48–72 hours after) and is clinically reviewed in a clinic within 2–3 weeks. Further PROMs are collected in both groups at timepoint 4 (T4), which is 12 weeks after baseline, and 24 weeks (6 months) after baseline as the final timepoint 5 (T5). All children receive the same standard of care.

**Table 1 T1:** Outline of study procedures

Procedure undertaken	T1 (Baseline)	T1+1–2 weeks	T2 (T1+4–5 weeks)	T3 (T1+≥6 weeks)	T3+2–3 weeks	T4 (T1+12 weeks)	T5 (T1+24 weeks)
Screening for eligibility	**√ ∞**						
Informed consent	**√ ∞**						
Randomisation	**√ ∞**						
Medical history	**√ ∞**						
Medical chart review	**√ ∞**		**√ ∞**		**∞**		
Clinical assessment	**√ ∞**		**√**		**∞**		
PedsQL 4.0	**√ ∞**		**√ ∞**			**√ ∞**	**√ ∞**
DASS21	**√ ∞**		**√ ∞**			**√ ∞**	**√ ∞**
STAI QoL	**√ ∞**		**√ ∞**			**√ ∞**	**√ ∞**
PAC-QoL (if cough present)	**√ ∞**		**√ ∞**			**√ ∞**	**√ ∞**
Cough severity score (if cough present)	**√ ∞**		**√ ∞**		**∞**	**√ ∞**	**√ ∞**
Spirometry if able	**√ ∞**		**√**		**∞**		
FB		**√**		**∞**			
Post-FB phone call (48–72 hours post-FB)		**√**		**∞**			
BAL result review			**√**		**∞**		
Physician opinion on diagnosis and management	**√ ∞**	**√**	**√**	**∞**	**∞**		

^√^ = Early bronchoscopy group (intervention)

^∞^ = Normal-wait bronchoscopy group (control)

BAL, bronchoalveolar lavage; DASS21, depression, anxiety and stress scale; FB, flexible bronchoscopy; PAC-QoL, Parent-proxy Children’s Acute Cough-specific QoL; PedsQL 4.0, Pediatric Quality of Life 4.0; STAI QoL, State-Trait Anxiety Inventory Quality of Life; T1, timepoint 1; T2, timepoint 2; T3, timepoint 3; T4, timepoint 4; T5, timepoint 5.

### Further description of data collection

Data are collected from parent interview and from medical records. At baseline, demographic data, medical history, medications, tobacco smoke exposure, birth history and spirometry (if available) are recorded. The treating respiratory paediatrician undertaking the FB documents the child’s provisional expected FB findings and overall clinical diagnosis, indication for FB and proposed investigations and therapy before the FB at baseline (T1). Routine respiratory examination is also collected using standardised data collection sheets (eg, cough pointers; digital clubbing; chest wall deformity; ear, nose and throat; and auscultation). On the day of the FB, parents are asked to rate their child’s cough using validated score^27^ (which is repeated in the post-FB clinic follow-up appointment), if cough is present. After the FB has been undertaken, the treating physician documents the following:

The FB and overall clinical diagnosisWhether FB leads to confirmation or exclusion of provisional diagnosisIf there is a new diagnosis and if confirmation of provisional FB diagnosis changed managementIf exclusion of provisional FB diagnosis has reassured the clinician and/or family and/or changed existing management

The a priori definition of change in management (defined below) is documented after FB. The CT of the chest (if one is done concurrently, ie under the same general anaesthetic as the FB) diagnosis is also recorded, and if any management was new or changed due to the CT result is also recorded so as not to have this as a confounding variable. The physician fills in three 10-point Likert point questionnaires (1=not at all, 10=very much) regarding the FB contribution to diagnostic clarity, therapeutic management and education or counselling of parent(s) (how much did the FB contribute to the diagnostic clarity in this case, how much did the FB increase confidence in the therapeutic management of the child and how much did the FB aid in educating/counselling the parent/guardian). Complications occurring during the FB procedure are also collected including laryngospasm, bronchospasm, nasal trauma/epistaxis (for transnasal approach), pneumothorax, pulmonary haemorrhage and/or if there is hypoxia which necessitates the removal of bronchoscope for bag-mask ventilation or intubation. The SpO2 nadir will also be recorded in this instance.

Parents are again contacted by phone call 48–72 hours post-FB to check if there were any fevers in the first 24 hours post-FB and/or if anything occurred which led them to seek medical attention (seeing their family doctor or going to an emergency department). The parent also fills out three 10-point Likert point questionnaires (1=not at all, 10=very much) regarding how much the FB has reduced their concerns or worries, how likely are they to undergo FB again in the future if clinically indicated and how likely are they to recommend FB to another family who has had the same respiratory issue.

In the medical appointment at post-FB (2–3 weeks post-FB in the control and intervention groups), the parents/guardians of both groups are asked two more 10-point Likert questions:

How much has their child improved after bronchoscopy?How much knowing the results of FB+BAL reduced their concerns or worries?

Three 10-point Likert point questionnaires are also filled in by the physician as aforementioned, but this time as regards to both the FB and BAL’s (previous questions were only regarding the FB, immediately after the FB, whereas in the clinic, the BAL results would be available as well) contribution to diagnostic clarity, therapeutic management and education or counselling of parent/guardian and if the results of FB and/or BAL have changed management at this point in time.

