### Endpoints

The primary endpoint is a change in QoL determined by the PedsQL 4.0 between the two arms at T2 (figure 1) (prior to control group having their FB) and the baseline (T1). The secondary endpoints are as follows: (a) proportion of children whereby FB changes clinical management based on a priori factors, (b) change in DASS21 scores (T2 minus T1), (c) change in PAC-QoL scores (including cough severity scores) (T2 minus T1), (d) change in STAI scores (T2 minus T1), (e) Likert scores reflecting opinions relating to the benefit of FB (patient and doctor perspective) in clinical practice and (f) change in PedsQL 4.0, DASS21, PAC-QoL (including cough severity score) or STAI in T4 and/or T5 (to examine if there is any sustained effect by the intervention (FB)).

A priori definitions of change in management are as follows:

Decision to admit for intravenous antibiotics and physiotherapy directly after FB. This will be based on the secretion score^29^ and the secretion colour which is part of a validated FB bronchitis score (Bscore)^37^ (see figure 2 for details of the management pathway). The importance of this management strategy in improving clinical outcomes has been previously highlighted by research findings.^38 39^
Started oral (PO) antibiotics directly after FB (excluding azithromycin for CT scan-proven BE). This will also be based on the secretion score,^29^ which is part of the Bscore^37^ (see figure 2 for details of the management pathway).Change in type of intravenous or PO antibiotics (or change from oral to intravenous) after BAL culture results are available(eg, anti-pseudomonal antibiotics for *Pseudomonas aeruginosa*).Referred to another specialty for appropriate management changes for intervention based on findings on FB. Examples include referral to surgeons such as cardiothoracic (eg, for vascular ring), ENT (eg, subglottic lesion) and paediatric (eg, tracheo-oesophageal fistula) surgeon.

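### Adverse events are missing from the endpoint list, and fever and unscheduled care are asked about only after each child's own bronchoscopy, with no matching question for waiting controls before T2

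*Protocol article*

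**What the plan says.** The abstract of the protocol article states: "Our secondary outcomes are change in management, change in PROMs, adverse events and the Likert scales". The Introduction gives part of the reason for the trial as the need to "define the efficacy, benefits and adverse events associated with elective FB in the diagnosis and management of children". The Endpoints section opens its list with "The secondary endpoints are as follows: (a) proportion of children whereby FB changes clinical management based on a priori factors" and continues to item (f). It covers management change, the questionnaires at T2, the Likert scores and the later questionnaires. No item concerns adverse events.

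The section Further description of data collection gives two sources of adverse-event data.

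- **During FB:** "Complications occurring during the FB procedure are also collected including laryngospasm, bronchospasm, nasal trauma/epistaxis", followed by further named events and by a check "if there is hypoxia which necessitates the removal of bronchoscope for bag-mask ventilation or intubation", with the saturation nadir recorded in that case.
- **Telephone call 48–72 hours after FB:** one item is "to check if there were any fevers in the first 24 hours post-FB"; the other is "if anything occurred which led them to seek medical attention (seeing their family doctor or going to an emergency department".

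Table 1 places the call after each arm's own FB: at one to two weeks in the early arm, and from six weeks in the control arm. T2 falls at four to five weeks, before the controls have FB. Table 1 marks medical chart review for both arms at T2. Details of safety monitoring are referred to supplemental file 1, which is not shown.

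**The concern.** T2 is the one time at which the trial compares children who have had FB with randomised children who have not. The primary outcome uses that contrast. Fever and visits to a doctor or emergency department also occur without FB in children under investigation for respiratory disease. A count of such events after FB, with no equivalent count in waiting children over the same period, mixes any effect of the procedure with the background rate.

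At stake is the harm side of the trial's conclusion. Benefit would be reported as a randomised difference, whereas non-specific harm would be a single-group count. Omission from the endpoint list adds to this, because it leaves open whether adverse events will be reported as a secondary outcome at all.

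**Working it through.** The documents give no adverse-event rate and no calculation for this outcome, so there is no figure to reproduce. The check sets the sections side by side and then asks how precise a comparison would be.

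**1. Outcome lists.** The abstract includes adverse events. Endpoints (a) to (f) do not. The secondary aims under Study objectives and hypothesis, and the secondary outcomes restated in the Discussion, omit them too.

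**2. What is asked, of whom, and when.**

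| Event type | Early arm, by T2 | Control arm, by T2 |
|---|---|---|
| Procedural complications | Recorded at FB | Cannot occur yet |
| Fever | Asked at the call, first 24 hours only | No question stated |
| Medical attention sought | Asked at the call, up to 48–72 hours | No question stated |
| Medical chart review | Scheduled | Scheduled |

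The gap is in rows two and three. Row four is a possible partial substitute, but the article does not say that adverse events are extracted from the chart.

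**3. Length of the windows.**

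- Fever: a call at 48 hours leaves 48 − 24 = 24 hours unasked (24/48 = 50%). A call at 72 hours leaves 72 − 24 = 48 hours (48/72 = 67%). These are shares of clock time, not of events. Fever in that time is still caught if it led to medical care.
- From the call (day 2–3) to the post-FB clinic (day 14–21): 14 − 3 = 11 to 21 − 2 = 19 days with no dedicated adverse-event question stated.

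**4. Precision of a comparison by arm at T2.** Inputs are 57 per arm enrolled and 48 per arm after dropout (Sample size section). The event rates are assumptions.

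If both arms have rate p, the 95% CI half-width for the difference is 1.96 × √(2p(1 − p)/n):

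- p = 5%, n = 57: 1.96 × √(2 × 0.05 × 0.95/57) = 8.0 percentage points; n = 48: 8.7.
- p = 10%, n = 57: 1.96 × √(2 × 0.10 × 0.90/57) = 11.0 percentage points; n = 48: 12.0.

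The early-arm rate detectable with 80% power (two-sided α = 0.05) solves [|p₁ − p₂| − 1.96√(2p̄(1 − p̄)/n)] / √[(p₁(1 − p₁) + p₂(1 − p₂))/n] = 0.84, where p̄ is the mean of p₁ and p₂:

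| Assumed control rate | n = 57 per arm | n = 48 per arm |
|---|---|---|
| 1% | 15% | 17% |
| 5% | 23% | 25% |
| 10% | 31% | 33% |

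**5. Procedural events.** These need a denominator, not a comparator. If no event of one type is seen in N procedures, the one-sided 95% upper bound is 1 − 0.05^(1/N): 2.6% for N = 114 and 3.1% for N = 96.

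**The case against.** A reader might go further and infer that harm from FB is under-counted, that there is no comparator at all at T2, and that deterioration while waiting goes unseen. The documents do not support these readings.

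- **Procedural harm is collected.** The list opens with a non-exhaustive word, and such events cannot occur in a child who has not had FB.
- **The 24-hour limit applies to fever alone.** The question about medical attention runs to the call.
- **The period after the call is not blind.** Table 1 schedules clinical assessment and chart review at the post-FB clinic in both arms. The 11 to 19 days lack a stated dedicated question; events in them may still be seen.
- **Waiting controls are observed.** They repeat the questionnaires at T2 and have chart review then. A need for urgent FB is an exit criterion.
- **Net under-counting is not shown.** The short fever window can miss late fever, but without a comparator, background fever and visits may be attributed to FB. The two work in opposite directions.
- **Minor symptoms.** The Introduction lists "hypoxia, nausea, vomiting, headaches, confusion and unscheduled hospitalisation" among the risks, and several of these have no question unless care was sought. Whether to ask about self-limiting symptoms is a matter of preference, and I do not press it.
- **An unseen source.** Supplemental file 1 may describe further adverse-event collection.

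It is also fair to say that the remedy comes late and that 57 per arm is small. These objections narrow the point. They leave standing the conflict between abstract and endpoint list, and the lack of a stated matching question on fever and unscheduled care in controls before T2. A supplement could supply the question, but it would not reconcile the two lists in the article.

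**Conclusion.** The point holds in a limited form. The article contradicts itself on whether adverse events are a secondary outcome. For fever and unscheduled medical attention, it states questions that follow FB and none for waiting controls over the same period, so the only randomised contrast between FB and no FB yet is not used for these events. The effect on the reported rates cannot be sized, because no event rate is given, and its direction is not established.

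This is a modest weakness in the safety reporting and does not touch the primary endpoint. It rests on two assumptions: that supplemental file 1 adds no matching collection in controls, and that the T2 chart review is not already used to extract these events. If either is wrong, what remains is the mismatch between the two lists.

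**What to change.** 1. Check supplemental file 1 first for adverse-event collection already in place, and summarise it in the main text.
2. Add adverse events to the Endpoints list. For procedural events, use all children in whom FB was attempted as the denominator. This matters because a severe FB-related event that prevents completion is an exit criterion, and a denominator of completed procedures would drop those children.
3. At T2, ask both arms the same two items, covering the time since T1: any fever, and any unscheduled family-doctor, emergency or hospital contact. Report them descriptively by randomised arm with 95% CI and no claim of adequate power.
4. For children already past T2, take unscheduled contacts from the T2 chart review scheduled for both arms, applying the same extraction rule to each. State that fever at home and family-doctor visits may be incomplete.

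**Cost.** Item 2 needs no new data. Item 3 adds two questions to an existing contact and needs a form amendment, with minor burden for parents. Data will be partial: recruitment was due to end in late 2023 and T2 comes four to five weeks after enrolment, so on that timetable most children rely on item 4. Precision stays low, as the intervals in the working show.
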